# Evaluating the effectiveness of early urethral catheter removal combined with intermittent catheterization for promoting early recovery of bladder function after laparoscopic radical hysterectomy: a study protocol for a randomized controlled trial

**DOI:** 10.1186/s13063-024-08266-8

**Published:** 2024-06-28

**Keywords:** Radical hysterectomy, Intermittent catheterization, Indwelling catheters, Bladder function, Randomized controlled trial

## Abstract

**Background:**

Bladder dysfunction, notably urinary retention, emerges as a significant complication for cervical cancer patients following radical hysterectomy, predominantly due to nerve damage, severely impacting their postoperative quality of life. The challenges to recovery include insufficient pelvic floor muscle training and the negative effects of prolonged postoperative indwelling urinary catheters. Intermittent catheterization represents the gold standard for neurogenic bladder management, facilitating bladder training, which is an important behavioral therapy aiming to enhance bladder function through the training of the external urethral sphincter and promoting the recovery of the micturition reflex. Nevertheless, gaps remain in current research regarding optimal timing for intermittent catheterization and the evaluation of subjective symptoms of bladder dysfunction.

**Methods:**

Cervical cancer patients undergoing laparoscopic radical hysterectomy will be recruited to this randomized controlled trial. Participants will be randomly assigned to either early postoperative catheter removal combined with intermittent catheterization group or a control group receiving standard care with indwelling urinary catheters. All these patients will be followed for 3 months after surgery. The study’s primary endpoint is the comparison of bladder function recovery rates (defined as achieving a Bladder Function Recovery Grade of II or higher) 2 weeks post-surgery. Secondary endpoints include the incidence of urinary tract infections, and changes in urodynamic parameters, and Mesure Du Handicap Urinaire scores within 1 month postoperatively. All analysis will adhere to the intention-to-treat principle.

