## Interventions

### Explanation for the choice of comparators {6b}

In the control group, catheters will be removed seven days post-operation as determined by the attending physician. If residual urine volume (RUV) exceeds 100 mL upon catheter removal, this will indicate urinary retention, promoting reinsertion of the catheter. The catheter will be removed on a weekly basis thereafter, until RUV is less than 100 mL [22–24].

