### Intervention description {11a}

Health education (preoperative): Prior to the surgery, patients and their family members will be provided with education on IC. This will include an overview of the principles, methodology, and procedural steps of IC, complemented by instructional videos.Supervision and guidance (postoperative days 1–2): Study team members will provide supervision and guidance to patients regarding pelvic floor muscle training (PFMT). Continued education on IC will be delivered through instructional videos to patients and their families.Catheter removal process (postoperative day 3): Following the prescribed fluid intake plan, IDUCs will be removed according to the physician’s instructions. Patients will be encouraged to urinate spontaneously 2–3 times within 2 h of catheter removal. After the last voiding, RUV will be immediately assessed via ultrasound. If RUV exceeds 100 mL, IC will be initiated. The frequency of IC will be adjusted based on RUV. When the frequency of catheterization decreases to once per day and RUV is less than 100 mL after spontaneous urination, bladder voiding function will be considered to be recovered to level II or higher.Patient ability to perform IC will be evaluated by the pencil and paper test [25]. The total score is 15 points, with a score ≥ 9 points indicating patient can perform IC with assistance from medical staff or family. Those scoring < 9 points will require direct assistance from medical staff.Scheduling of IC: The frequency of IC will be tailored according to RUV measurements: 5–6 times daily for RUVs of 350–500 mL (5 times per day: 7:00, 11:00, 15:00, 19:00, 22:00; 6 times per day: 7:00, 11:00, 15:00, 19:00, 22:00, 1:00); 3–4 times daily for RUVs of 200–350 mL (3 times per day: 7:00, 13:00, 19:00; 4 times per day: 7:00, 13:00, 19:00, 22:00); 1–2 times daily for RUVs of 100–200 mL (once per day at 19:00; twice per day at 7:00 and 19:00). Specific timing for catheterization is outlined.Drinking plan: Total daily fluid intake is set 1500–2000 mL, and not exceed 2500 mL [12, 13]. Drink 400–500 mL of each meal (including intravenous infusion, liquid beverages, milk, soup). Between meals, patients may drink 200–300 mL of fluids every time. Fluids should be avoided from 20:00 to 6:00.Voiding diary for IC: Participants will record intake amounts (including intravenous infusion volume during hospitalization), spontaneous voided volume, urination times, IC interval, catheterized volume, uresiesthesia and symptoms over a continuous 24-h period. Milliliter was used for fluid unit. And fluid volume was determined by professional tools.Bladder training: Exception pelvic floor rehabilitation training, patients undergoing IC will participate in bladder training, which includes scheduled urination, urge suppression, and compensatory voiding maneuvers to enhance urinary behavior.

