### Relevant concomitant care permitted or prohibited during the trial {11d}

All participants enrolled in the study will receive essential baseline care throughout the study, including pelvic floor rehabilitation training starting 6 h post-operation and continue for up to 3 months [26].

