#### Secondary outcomes

Urinary tract infection within the first month post-surgery [28]. Patients have symptoms, including urinary urgency, frequency, pain, or other urinary irritation symptoms, as well as lower abdominal tenderness, flank tenderness, and potentially with or without fever. Diagnosis is confirmed by finding white blood cells ≥ 10/ high power field in urine examinations, coupled with urine cultures in catheterized patients.Bladder dysfunction within three months post-surgery: Assessed using the Mesure Du Handicap Urinaire (MHU) bladder function scale for self-assessment.Changes in urodynamic parameters within 1 month post-surgery: This involves comparing urodynamic measurements, including maximum flow rate, average flow rate, RUV, bladder safe capacity, maximum detrusor pressure, and bladder compliance.

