## Data collection and management

### Plans for assessment and collection of outcomes {18a}

Outcome assessments will be meticulously documented by the research evaluator on the case report form (CRF), identifying participants by their study ID numbers and initials, thus ensuring confidentiality. Baseline assessments will be conducted prior to surgery. Evaluations for postoperative urinary tract infection are scheduled at 3 days, 1 week, 2 weeks, 3 weeks, and 4 weeks post-surgery. Assessments for bladder dysfunction post-operation will occur at 1 week, 2 weeks, 3 weeks, 1 month, and 3 months post-surgery. Urodynamic results will be collected 1 month post-surgery. Follow-up will be conducted through WeChat APP or telephone.

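### The UTI endpoint counts infections from surgery, so those present at the day-3 evaluation, when both arms have had the same indwelling catheter, dilute the comparison (minor)

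*Protocol article*

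**What the plan says.** The abstract lists UTI among the secondary endpoints with a one-month window: "Secondary endpoints include the incidence of urinary tract infections, and changes in urodynamic parameters, and Mesure Du Handicap Urinaire scores within 1 month postoperatively". The abstract sentence does not say when counting starts. That comes from Outcomes {12}, Secondary outcomes: "Urinary tract infection within the first month post-surgery".

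The section on collection of outcomes {18a} gives the visits: "Evaluations for postoperative urinary tract infection are scheduled at 3 days, 1 week, 2 weeks, 3 weeks, and 4 weeks post-surgery". It also says "Baseline assessments will be conducted prior to surgery", so day 3 is an outcome reading and not a baseline.

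The catheter schedules are in two places:
- Intervention description {11a}: "Catheter removal process (postoperative day 3): Following the prescribed fluid intake plan, IDUCs will be removed".
- Choice of comparators {6b}: "catheters will be removed seven days post-operation as determined by the attending physician".

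Nothing in the article removes infections found on day 3 from the endpoint, reports them separately, or restricts the endpoint to new onset. The section on additional analyses {20b} plans none.

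**The concern.** The trial compares two catheter strategies that differ only from postoperative day 3. Before then, the intervention text adds education on intermittent catheterization and supervised pelvic floor training. Concomitant care {11d} gives all participants baseline care, "including pelvic floor rehabilitation training starting 6 h post-operation". Nothing described for the first days would be expected to change infection risk in one arm and not the other.

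An infection found on day 3 therefore carries no information about the strategies, yet it counts as an event in whichever arm it falls. The Discussion expects early removal to lower UTI by shortening indwelling time, and that mechanism can act only after day 3. If early infections are common enough, a real relative reduction looks smaller than it is and is more easily missed.

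**Working it through.** **Inputs from the protocol.** Sample size {14} gives 35 per arm, raised to 39 for dropout: 35 / (1 − 0.10) = 38.9, so 39. Statistical methods {20a} gives a chi-square test for count data at p < 0.05. There is no UTI rate and no sample-size figure for UTI, so the plan has no number of its own to reproduce here.

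**Assumptions.**
- All 39 per arm are analysed.
- A fraction b of each arm has UTI by the day-3 evaluation, equal in expectation in the two arms. Values used: 1, 2, 5 and 10%. With 39 per arm these are 0.39, 0.78, 1.95 and 3.9 patients per arm.
- Patients free of UTI on day 3 have later risk c (control) or t (intervention). Pairs used: 20% vs 8%, 25% vs 10%, 30% vs 12%; each has t/c = 0.40.
- A patient infected on day 3 has no second, new UTI within the window.

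**Formulas.**
- Count from surgery: control b + (1−b)c; intervention b + (1−b)t.
- New onset after day 3, all randomised in the denominator: (1−b)c and (1−b)t.
- Risk difference: (1−b)(c−t) under both counts.
- Risk ratio: t/c = 0.40 for new onset; closer to 1 for the count from surgery.

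**One case in full (25% vs 10%, b = 5%).**
- From surgery: 0.05 + 0.95 × 0.25 = 28.75%, and 0.05 + 0.95 × 0.10 = 14.5%. Risk ratio 0.145 / 0.2875 = 0.50.
- New onset: 0.95 × 0.25 = 23.75%, and 0.95 × 0.10 = 9.5%. Risk ratio 0.40.
- The risk difference is 14.25 points either way. In the count from surgery, 5 of the intervention arm's 14.5 points, about a third, predate any difference in catheter care.
- The standard error of the difference is √[(0.2875×0.7125 + 0.145×0.855)/39] = 9.2 points from surgery and √[(0.2375×0.7625 + 0.095×0.905)/39] = 8.3 points for new onset. The power gain comes from this.

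**Power.** Exact enumeration of the two-sided pooled chi-square test, 39 per arm:

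| Later risks | b | Counted from surgery | RR | Power from surgery | Power new onset | Gain (points) |
|---|---|---|---|---|---|---|
| 20% vs 8% | 1% | 20.8% vs 8.9% | 0.43 | 32.5% | 34.4% | 2.0 |
| | 2% | 21.6% vs 9.8% | 0.46 | 30.5% | 34.1% | 3.7 |
| | 5% | 24.0% vs 12.6% | 0.53 | 25.8% | 33.2% | 7.4 |
| | 10% | 28.0% vs 17.2% | 0.61 | 20.9% | 31.8% | 10.9 |
| 25% vs 10% | 1% | 25.8% vs 10.9% | 0.42 | 40.5% | 42.2% | 1.7 |
| | 2% | 26.5% vs 11.8% | 0.45 | 38.5% | 41.8% | 3.3 |
| | 5% | 28.8% vs 14.5% | 0.50 | 33.8% | 40.6% | 6.8 |
| | 10% | 32.5% vs 19.0% | 0.58 | 28.3% | 38.6% | 10.3 |
| 30% vs 12% | 1% | 30.7% vs 12.9% | 0.42 | 49.0% | 50.5% | 1.4 |
| | 2% | 31.4% vs 13.8% | 0.44 | 47.3% | 49.9% | 2.7 |
| | 5% | 33.5% vs 16.4% | 0.49 | 42.6% | 48.4% | 5.8 |
| | 10% | 37.0% vs 20.8% | 0.56 | 36.3% | 45.9% | 9.6 |

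The gain is 1.4 to 3.7 points at 1–2% early UTI, and 5.8 to 10.9 points at 5–10%.

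**The case against.** The strongest reply is that this is a legitimate estimand. Patients are allocated on signing consent, and total UTI in the month after surgery is a cumulative incidence under intention-to-treat that also answers a patient's question. Early infections are balanced in expectation. This stands: a reader might infer that the comparison is biased or invalid, and the protocol does not support that. The fix does not even change the expected risk difference.

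A second reply is that early infections may be rare. The definition in {12} requires symptoms and white cells in the urine, with culture in catheterized patients, so asymptomatic bacteriuria on day 3 would not count. Nothing in the protocol supports 5–10%. This also stands, and it is why the 1–2% rows are shown.

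A third is that the visits already planned allow a post-day-3 tabulation, and an analysis plan may contain one. That is true of the data. But the protocol itself fixes the window and the visit schedule and plans no additional analysis, so stating the choice there is still worthwhile.

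Finally, the split at day 3 is imperfect. An infection seeded under the shared catheter may show only on day 4 or 5 and would count as new. Dating onset also matters more when participants and staff know the allocation and the definition rests partly on reported symptoms. These limits argue for keeping the from-surgery total in the report; they do not remove the dilution.

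**Conclusion.** The concern holds as a minor point. Infections present on day 3 are uninformative events in a secondary endpoint. They move the risk ratio toward 1 and cost some power, without biasing the randomised comparison.

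The size rests on assumed rates. With a true later risk ratio of 0.40, the counted ratio becomes 0.42 to 0.46 at 1–2% early UTI and 0.49 to 0.61 at 5–10%. The recoverable power is about 1 to 4 points and 6 to 11 points respectively.

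Two stronger readings should be avoided:
- Comparing the from-surgery count with a population that has no early UTI suggests a loss of 8 to 15 points at 5–10%. That overstates what the change buys, because day-3 cases stay in the denominator as non-events.
- UTI is not the trial's only record of harm. Adverse event reporting {22} records all adverse events and names severe urinary retention and hydronephrosis as well.

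Power for UTI stays low in every scenario, at most about 50% with the fix. The trial was sized on bladder recovery at 2 weeks, and that conclusion is untouched.

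**What to change.** Amend the outcome definition and the assessment schedule as follows:
1. Record the day-3 UTI evaluation before the catheter is removed in the intervention arm, and at the same time point in control. The article does not state this order.
2. Prespecify new-onset UTI after that evaluation and up to 4 weeks as the comparison of the strategies, with all randomised patients in the denominator.
3. Report infections present on day 3 by arm, and the from-surgery one-month total beside the new-onset result.

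The cost is a sentence or two; the day-3 visit is already scheduled and no new data are needed. The downsides are slightly fewer counted events and more reliance on dating onset in an open-label trial. Because recruitment has begun, make the change before outcome data are examined by arm.

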**Discussion:**

The findings from this trial are expected to refine clinical management strategies for enhancing postoperative recovery among cervical cancer patients undergoing radical hysterectomy. By providing robust evidence, this study aims to support patients and their families in informed decision-making regarding postoperative bladder management, potentially reducing the incidence of urinary complications and improving overall quality of life post-surgery.

**Trial registration:**

ChiCTR2200064041, registered on 24th September, 2022.

## Administrative information

Note: the numbers in curly brackets in this protocol refer to SPIRIT checklist item numbers. The order of the items has been modified to group similar items (see http://www.equator-network.org/reporting-guidelines/spirit-2013-statement-defining-standard-protocol-items-for-clinical-trials/).

Role of sponsor {5c}	This is an investigator-initiated study and the sponsor is involved in study design, data collection and analyses as well as manuscript preparation.

## Introduction

### Background and rationale {6a}

Cervical cancer remains a significant challenge to global public health. According to the WHO’s International Agency for Research on Cancer (IARC) 2020 data [1], there were 604,127 new cases of cervical cancer and 341,831 deaths worldwide. Radical hysterectomy (RH), coupled with pelvic lymphadenectomy, is standard treatment for early-stage cervical cancer [2, 3]. However, this surgical intervention often results in bladder dysfunction due to nerve damage, leading to impaired urination control and neurogenic bladder (NB) [4, 5]. The reported incidence of post-surgical bladder dysfunction varies widely, ranging 12 to 85% [6–8]. Symptoms include urinary retention, dysuria, incomplete urination, and urinary incontinence, with urinary retention being the most prevalent [9]. These symptoms elevate the risk of serious complications such as postoperative urinary tract infections, hydronephrosis, bladder rupture, increased rates of outpatient visits, and hospital readmissions [10, 11]. Factors contributing to impaired recovery of bladder function include insufficient pelvic floor muscle training and prolonged postoperative indwelling urinary catheters (IDUCs), which affect the bladder’s natural filling and emptying processes.

Clinical studies have demonstrated that the potential for full restoration of bladder function within 9–12 months post-surgery is through comprehensive lower urinary tract management, focusing particularly on the bladder [6]. Postoperative bladder dysfunction management includes pharmacological treatments such as acetylcholine release stimulants and α-adrenergic receptor blockers, as well as non-pharmacological interventions like intermittent catheterization (IC) and bladder training, which are noted for their simplicity, minimal invasiveness, and low side effects [5]. IC, the periodic emptying of the bladder using a catheter, is supported by class A evidence in NB management and is considered the gold standard [12]. Bladder training, a behavioral therapy aiming to improve bladder function and establish regular urination, has proven effective in preventing post-RH bladder dysfunction and is recommended in nursing practice guidelines for NB management [13]. While there is no consensus on the optimal time for IDUCs removal post-RH, the typical practice varies from 3 to 14 days influenced by hospital policy, surgeon preference, and experience, with potential delays in removal [14, 15]. Some studies advocate for IC to post-catheter removal to manage urinary retention maintaining moderate intravesical pressure to minimize complications, and improve both bladder function rehabilitation and patient quality of life [12, 16].

Despite retrospective studies have compared the application effectiveness of early postoperative catheter removal combined with IC for bladder function recovery [17–20], these studies lack the assessment of subjective symptoms of bladder dysfunction in cervical cancer patients post-RH. This highlights the need for further high-quality randomized controlled trials (RCT) to reassess these strategies. Therefore, this study intends to compare early urinary catheter removal (3 days post-surgery) followed by IC in patients with grade II or lower bladder function recovery against conventional IDUCs approaches in a randomized parallel-controlled trial. By establishing a reasonable hydration plan to stabilize urine production, this trial aims to facilitate bladder training and promote urination reflex recovery. The primary objective of this study is to evaluate the effectiveness and safety of this intervention, offering a new active bladder function management post-RH.

### Objectives {7}

The primary objective of this study is to evaluate the effectiveness and safety of early urinary catheter removal combined with IC in restoring bladder function among patients with cervical cancer post-RH, as compared to standard care with IDUCs.

### Trial design {8}

This study is a parallel-group superiority randomized controlled trail conducted at a single center, with an allocation ratio of 1:1. We hypothesize that early urinary catheter removal combined with IC is superior in terms of efficiency and effectiveness compared to IDUCs. All participants in the study will be assessed weekly and followed for 3 months. The flow chart is shown detailing the study design, and all interventions and outcome measures are presented in Fig. 1 and Table 1 respectively. This trial follows the report standard of SPIRIT 2013.

**Fig. 1 Fig1:**
[figure not shown]
The Flowchart of the study. IDUCs: indwelling urinary catheters, IC: intermittent catheterization

**Table 1. Tab1:**
[figure not shown]
Enrolment and outcome measurements

## Methods: participants, interventions, and outcomes

### Study setting {9}

All participants are recruited from the First Affiliated Hospital of Army Medical University of PLA in Chongqing, China. The Ethics Committee of this hospital has approved this study protocol, (Approval No.(A)KY2021113)). All potential participants will sign a written informed consent form before allocation.

### Eligibility criteria {10}

#### Inclusion criteria

→Prospective enrolment of patients diagnosed with cervical cancer stages IA1 (infiltration of lymphatic vasculature space), IA2, IB1, IB2, and IIA1, according to the FIGO 2018 classification [21].→Patients underwent Laparoscopic RH and pelvic lymphadenectomy.→Aged 20 to 65 years, and BMI < 30 kg/m^2^.→Classified as I or II under the American Society of Anesthesiologists (ASA) classification.→A score of more than 75 points on the preoperative Barthel self-care ability assessment.

#### Exclusion criteria

→Patients with pre-existing urinary dysfunction diseases, kidney diseases, or serious underlying conditions, such as uncontrolled severe anemia, hypertension, diabetes, and cardiovascular or cerebrovascular complications.→Surgical duration exceeding 4 h, or the blood loss surpassing 1000 mL.→Intraoperative injuries to the ureter, bladder, or bowel; Postoperative complications such as vesicovaginal or urethrovaginal fistulas→Conditions requiring emergency intervention or reoperation within 6 h post-operation→Patients with severe mental illness, or cognitive dysfunction.→

#### Exit criteria

→Participants are reluctant to continue the study.→If researchers believe that continued participation would be detrimental to patient treatment.

### Who will take informed consent? {26a}

Patients meeting the above inclusion criteria will be informed about this study after admission. Interested patients will attend an orientation session and be allocated a handbook regarding postoperative bladder management before surgery. Participants, who can review and complete consent independently will then be provided with the informed consent form. Those who agree to participate will sign a written informed consent form prior to enrollment.

